### Comparison condition

Parent-child pairs in comparison sites will receive usual care (standard BGC programming) during the study and the intervention upon study completion. BGCs deliver health and life skills programs each year on a variety of topics determined by each site (e.g., cyber-safety, substance use prevention). Comparison sites will continue to implement such programs but will refrain from implementing obesity-specific programs. Upon completion of data collection, the study team will train BGC staff in comparison sites to deliver the H_2_GO! intervention and provide intervention toolkits and protocols.

### Measures

#### Primary outcome

The primary outcome is change in child zBMI (number of standard deviations by which a child differs from the mean BMI of children of the same age and sex) over 12 months, an appropriate measure of that allows for comparing children of different ages over time as they grow [50]. Children’s height and weight will be used to calculate BMI, age- and sex-specific BMI percentiles, zBMI, and standard BMI-based weight status categories using CDC growth charts [51]. Trained BGC and study staff will take the average of two measurements of children’s height and weight using a stadiometer and a medical quality scale, respectively. Children will be measured in a private setting wearing light clothing (e.g., without shoes and heavy outer layers). Secondary outcomes and covariates for parent and child participants are summarized in Table 2 and are based upon validated instruments and surveys [52–61].

**Table 2 Tab2:** Secondary Outcome and Covariate Measures

Child Outcomes (self-report)	
SSB and water consumption *(secondary outcomes)*	A 15-item beverage intake questionnaire (BEVQ) will be used to assess frequency and amount of SSB and water consumption and energy intake (kcalories) from SSBs. The BEVQ has demonstrated reliability and validity in assessing beverage intake against 24-h recalls among youth [52].
Beverage intake self-efficacy	Self-efficacy to reduce SSB intake and increase water intake will be assessed using items from a nutrition self-efficacy scale validated among youth ages 8–11 years [53].
Diet	Frequency of consuming specific foods/food groups (e.g., vegetables, fruits, fast food, desserts) will be assessed using items from the School Physical Activity and Nutrition (SPAN) monitoring system [54]. These items have been validated for use by children in grades 4 and higher and were selected for their brevity and low response burden.
Physical activity	Time spent outdoors [55] and number of days during the past week children participated in ≥ 60 min of moderate-to-vigorous physical activity [56] will be used to assess child physical activity.
Screen time	Hours/day watching TV away from school (on TV or through a mobile or computer device) and hours/day playing video or computer games or using a computer for something other than schoolwork (including time on the Internet, instant messaging) away from school [54] will be used to assess screen time.
Youth empowerment	The 8-item Sociopolitical Control Scale for Youth (SPCS-Y) [57], which has been validated as a measure of empowerment among urban youth [58], will be used to assess youth empowerment. The SPCS-Y uses a 10-point, phrase completion response format and consists of a leadership/competence subscale and a policy/social control subscale [59].
Socio-demographics	Child gender, age, and race/ethnicity will be assessed via brief survey items.
**Parent Outcomes (self-report)**	
SSB and water consumption	Items from the beverage intake questionnaire (BEVQ-15) [60] assessing frequency and amount of beverages consumed will be used to assess SSB and water intake and SSB energy intake. The BEVQ-15 has been validated against 24-h dietary recalls among adults, including low-literacy populations [60].
Home SSB availability	One survey item assessing how often SSBs are available at home (5-point Likert scale ranging from “never” to “always”) [61] will be used to measure SSB home availability.
Socio-demographics	Gender, age, race/ethnicity, education, income, occupation, and child eligibility for free/reduced priced lunch will be assessed via survey items.

### Statistical approach and power

Our sample size calculations (*N* = 45 parent-child pairs per each of the 10 sites) are based on the primary hypothesis that child participants in intervention sites will have reduced zBMI compared to child participants in comparison sites over 12 months. Our pilot study showed an effect size of 0.22 zBMI units over 6 months [36]. We powered our analysis to detect a minimum effect size of 0.1 units over 12 months (a conservative approach considering possible attenuation of effects over the doubling of study time period) and anticipate a 0.15 SD in both groups. A 0.1 effect size is reasonable for populations inclusive of healthy weight children; of studies targeting school-aged children including those of healthy weight, randomized SSB interventions have yielded 0.0–0.13 unit differences in zBMI over 12–18 months [62, 63], and childhood obesity prevention interventions have yielded 0.10–0.16 unit differences in zBMI over 12 months [64, 65]. We assume an intra-class correlation coefficient of 0.05 [66–68]. With α = 0.05 and a 75% retention rate, we can detect ≥0.1 unit difference in zBMI with over 80% power and 0.2 unit difference with over 90% power by enrolling a total of 450 parent-child pair participants.

### Recruitment and retention

We will utilize the following participant recruitment approaches previously tested in our pilot study (identify eligible child participants through the BGC electronic enrollment record system and in collaboration with BGC staff), which yielded > 95% recruitment rate in our pilot study. Proposed strategies to retain participants include collecting multiple forms of contact information from parent/caregiver participants at baseline, scheduling pre-determined study assessments at dates/times convenient for participants, providing options for online or phone follow-up assessments, implementing a tracking and reminder system, offering assistance and support for participating in study assessments, using email and social media contact approaches, and providing incentives of $20 gift cards per assessment.

### Data management and confidentiality

A number of procedures will be utilized to maximize data integrity and quality control procedures for data collection and data entry. Quality control measures implemented by the project data analysists will include detailed and unabmigious specifications for completion of each of the data collection forms, including rules for coding skipped questions, missing data, and/or refusals. Interim incremental data reviews will be performed on all data to compare data collectors and determine variations among observers in responses to questions on data forms. Computer algorithms will be written to check logic and identify internal inconsistencies.

Password-protected study databases and locked offices will be used to maintain data security to the highest extent possible. The key to identification of subjects will be kept in a separate and secure location. These data will be stored and managed on a secure server in a HIPAA-compliant data center with daily back-up. Data entry will be through the REDCapTM Data Capture System (Vanderbilt University). All databases and analytic files will be contained within the Biostatistics and Epidemiology Data Analytics Center (BEDAC) secure environment with access controlled through user-specific login and passwords.

### Planned statistical analysis

Distributions, descriptive statistics, and missing values will be examined for child zBMI. Bivariate analyses will compare intervention and comparison group characteristics using chi-square tests for categorical variables and t-tests for continuous variables. Any statistically notable (*p* < 0.1) imbalances that arise between groups will be adjusted for in multivariable analyses. Analyses will utilize an intent-to-treat approach, with each participant enrolled in the intervention site analyzed as part of the group.

To test our primary hypothesis that children in intervention sites will have decreased zBMI compared to children in comparison sites, we will apply generalized linear mixed models. The hierarchical structure of the data (repeated measures on youth nested within sites) will be modeled by including participant- and site-level random intercepts. A more complex covariance structure for repeated measures over time on participants (e.g. unstructured covariance) will be incorporated into the analysis if necessary. The main predictors of the model include study condition (intervention vs. control), all time points, and the interaction term between study condition and time points. Intervention effects will be evaluated over the entire study period by testing the interaction term of time and study condition, and by specifically comparing change from baseline to 12 months via a statistical contrast. We will also compare changes from baseline to earlier time points using this approach. Covariates associated with child zBMI (e.g., gender, race, other dietary intake, physical activity) will be examined for balance between groups and incorporated into multivariable analyses if imbalances (*p* < 0.1) occur. Potential moderating effects of gender, age, and race/ethnicity on intervention effects will be examined via a three-way interaction with the moderator, the study condition indicator and time. Should significant interaction terms emerge from the data, we will analyze and report intervention effects by appropriate subgroups (e.g., males vs. females). Participants with incomplete follow-up can be included in analyses, which are valid under a missing at random assumption. We will assess the likelihood of nonignorable missing data using a pattern mixture model.

To test our secondary hypothesis that children in intervention sites will have decreased SSB intake and increased water intake than children in control sites over 12 months, we propose to compare SSB and water intake using linear mixed models and similar approaches described in the primary hypothesis testing. Comparisons of group mean changes from baseline to 2 and 6 months will also utilize this approach. We will additionally examine changes in child self-efficacy, parental beverage intake, SSB home availability, and spontaneous changes in other BMI-related behaviors (other dietary intake, physical activity, screen time, sleep) over time and by study condition using methods described above. Finally, for our mediation hypothesis, we will first examine whether the pattern of change in youth empowerment over time differs by study condition via a statistical interaction using a linear mixed model. Next, we will examine whether patterns of change over time in primary and secondary outcomes depend on level of empowerment by incorporating an empowerment by time interaction. Finally, we will incorporate both interaction terms (study condition by time and empowerment by time) to determine if the intervention effect is partially or fully mediated by empowerment.

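### Covariates are chosen by baseline tests that ignore clubs (p<0.1), and adding them as time-fixed main effects would not adjust the change contrast they are meant to protect

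*Protocol article*

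**What the plan says.** Under Planned statistical analysis, the article states the screening rule twice.

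- For group characteristics in general, the two arms are compared "using chi-square tests for categorical variables and t-tests for continuous variables". The consequence follows at once: "Any statistically notable (*p* < 0.1) imbalances that arise between groups will be adjusted for in multivariable analyses".
- In the paragraph on the primary hypothesis, the candidates are "Covariates associated with child zBMI (e.g., gender, race, other dietary intake, physical activity"), and they "will be examined for balance between groups and incorporated into multivariable analyses if imbalances (*p* < 0.1) occur".

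The candidate list is open, since the named items are examples. The terms fixed for the primary model are given separately: "The main predictors of the model include study condition (intervention vs. control), all time points, and the interaction term between study condition and time points", together with random intercepts for participant and site. The primary comparison is a contrast of change from baseline to 12 months between conditions. No covariate and no stratum term is fixed in advance, and no covariate-by-time term is mentioned for adjustment. The secondary outcomes are to be analysed by similar methods, so the rule carries over to them.

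**The concern.** There are three separate problems.

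1. **The tests have the wrong error rate.** Ten clubs are randomised. A t-test or chi-square test on individual children treats 225 children per arm as independent, so its p-values are too small for any characteristic that varies between clubs. The site random intercept belongs to the outcome model; nothing extends it to the balance tests.
2. **The selection depends on the data.** Adjustment is useful when a covariate predicts the outcome. Under this rule a prognostic covariate is left out if its test gives p above 0.1, and a weak one enters if its test falls below. Correcting the tests for clustering would lower the false-flag rate but would not cure this.
3. **The adjustment may miss its target.** The primary comparison is of change over time. A covariate that takes one value per child and enters as a main effect shifts every visit equally, so it drops out of a change contrast.

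At stake is whether the covariate-adjusted primary and secondary analyses are specified in advance, and whether they do what the plan intends.

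**Working it through.** **Inputs.** From Statistical approach and power: 45 pairs per site, 10 sites, ICC 0.05, SD 0.15, 75% retention, difference 0.1. From Study design: one site per arm within each geographic stratum, hence 5 sites and 225 children per arm. From Planned statistical analysis: threshold p<0.1, taken as two-sided. *Assumption:* the documents give no ICC for any covariate. The 0.05 is stated for the sample size and is borrowed here, with a range.

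**The plan's own figure.** The article gives no false-flag rate. Its power statement, which uses the same inputs, reproduces. After 75% retention there are 33.75 per site. The design effect is 1 + 32.75 × 0.05 = 2.6375, and the effective number per arm is 168.75 / 2.6375 = 64.0. The standard error is 0.15 × √(2/64.0) = 0.0265, and 0.1 / 0.0265 = 3.77. Power is Φ(3.77 − 1.96) = 96.5% by the normal approximation, 90.8% with a t reference on 8 degrees of freedom and 80.2% on 4. All exceed the stated 80%.

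**False-flag rate of the balance tests.** With no true imbalance, the variance of the difference in arm means is larger than the test assumes by DE = 1 + (m − 1) × ICC, with m = 45. The rate is 2 × [1 − Φ(1.645 / √DE)].

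| Assumed covariate ICC | DE | 1.645/√DE | Flagged |
|---|---|---|---|
| 0 | 1.00 | 1.645 | 10% |
| 0.01 | 1.44 | 1.371 | 17% |
| 0.02 | 1.88 | 1.200 | 23% |
| 0.05 | 3.20 | 0.920 | 36% |
| 0.10 | 5.40 | 0.708 | 48% |

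Simulation of 10 sites × 45 at ICC 0.05 agrees: 36.0% for the t-test and 35.7% to 35.9% for the chi-square test.

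**Allowing for geographic strata.** If strata explain a fraction f of the between-site variance, that part cancels between the two sites of a stratum. The variance ratio becomes 3.2 − f × 45 × 0.05 = 3.2 − 2.25f.

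- f = 0.5: ratio 2.075, rate about 25% (simulation 26%).
- f = 1: ratio 0.95, rate about 9% (simulation 9%).

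**Effect of a main-effect covariate on the primary contrast.** Let ȳ(a,t) be the mean in arm a at visit t, x̄(a) the covariate mean in arm a, x̄ the overall covariate mean and β its coefficient. With complete data and equal site sizes, the adjusted mean is ȳ(a,t) − β[x̄(a) − x̄]. The correction is the same at every visit, so change from baseline to 12 months is ȳ(a,12) − ȳ(a,0), exactly the unadjusted value. With a visit-specific coefficient, the difference in change is corrected by (β₁₂ − β₀) × [x̄(1) − x̄(0)]. That is the adjustment an imbalance in a predictor of change calls for.

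In a simulated example with an imbalanced covariate related to change and a true effect of zero, the contrast was 0.150 unadjusted, 0.150 with the main effect and 0.024 with covariate-by-time terms. With 75% retention and dropout dependent on the covariates, assuming a between-child zBMI SD of about 1 and an SD of change of 0.15, adding the screened main effects moved the estimate by at most 0.0003 zBMI over 150 runs.

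**The case against.** The strongest reply is that the rule does little harm to the primary result. The core of the model is fixed (condition, time, their interaction, random intercepts, the 12-month contrast), and the cancellation shown above means that main-effect covariates barely move that contrast. Against a target difference of 0.1, a shift of 0.0003 is negligible. This stands. A reader might infer that chance chooses the primary result or seriously distorts it; the documents do not support that for time-fixed main effects.

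A reader might also take 36% as a property of this trial's covariates. It is not. It is conditional on a borrowed ICC, and the pairing by geography, with sites selected for comparable size and ethnic composition, may lower it. Nor can one say how many covariates would be flagged, because the list is open and neither their ICCs nor their correlations are given.

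A high flag rate also pushes towards adjusting for more covariates, which is nearer to the remedy than to the harm. That is fair, but it leaves selection by p-value in place.

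One may defend the screen as a guard against differential recruitment, since children are enrolled after unblinded site randomisation. Such imbalance is possible, but a p-value that ignores clubs cannot separate it from chance variation between clubs.

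A reader might infer that follow-up diet and activity would be entered. The text does not say so, and a balance check naturally concerns baseline values.

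Finally, a covariate list is often left to the analysis plan. Here, however, the protocol does not defer the matter: it states a selection rule, twice.

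**Conclusion.** The point holds as a fault in a stated rule. The balance tests ignore the unit of randomisation, and the selection follows observed p-values and not prognostic value. For a covariate with ICC 0.05 the false-flag rate is about 36% against the nominal 10%; it is 17% to 48% over ICC 0.01 to 0.10, and about 26% or 9% if strata absorb half or all of the between-site variance at ICC 0.05. These figures rest on 45 children in every site, a two-sided threshold and assumed covariate ICCs.

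If flagged covariates enter only as time-fixed main effects, the rule also fails at its own purpose: the primary estimate remains in effect unadjusted for the imbalance. That is ineffective adjustment and an unfixed covariate set, not a seriously biased primary estimate. The plan should be changed, but the trial's design is not in question.

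**What to change.** In Planned statistical analysis:

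1. Delete the baseline significance tests and both statements of the p<0.1 rule. Report baseline characteristics by arm descriptively.
2. Name in advance a short list of prognostic baseline covariates, for example race/ethnicity, age and gender, together with the geographic stratum. Enter them whatever balance is observed.
3. Include covariate-by-time terms, so that the contrast of change is adjusted.
4. If diet and physical activity are used as covariates, state that only baseline values enter, because the same section also analyses their changes as outcomes.

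The cost is wording and a few more model parameters; recruitment, measurement and sample size are untouched. If inference uses between-club degrees of freedom, fitting five strata would reduce these from 8 to 4. At unchanged variance, the power computed above would go from 90.8% to 80.2%, still above the stated 80%.

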### Study design

This study is an unblinded parallel-group cluster randomized controlled trial with *N* = 10 BGC sites randomized to the intervention or comparison status. Geographic location is used as a stratification variable; sites within each stratum are spaced > 5 miles apart to minimize contamination bias. One site within each stratum will be randomly assigned to the intervention and the other to a wait-list, usual care condition. The randomization will be conducted by the project statistician using computer-generated random numbers. We opted to use a stratified sampling scheme to increase balance of BGC characteristics between study arms and include a representative sample of BGCs to increase generalizability.

After sites are randomized, participants will undergo recruitment and enrollment and complete in-person study assessments at baseline, 2, 6, and 12 months follow-up (see Fig. 2). Comparison group participants will have study assessments scheduled to match the timing of each intervention cycle. To enhance adherence to intervention protocols, the study team will complete intervention fidelity and process measures of intervention sessions using intervention attendance, recruitment, and retention rates, as well as an intervention fidelity checklist to score completion of intervention activities (0 = did not do this activity; 1 = partially completed; 2 = completed) across each of the 12 intervention sessions. The study team will also monitor intervention sessions and provide corrective feedback and ongoing trainings and refresher sessions as needed. Intervention fidelity monitoring and corrective feedback processes will be completed remotely via Zoom when study staff were unable to be present onsite BGC due to COVID-19 restrictions.

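### The primary mixed model has no site-by-time term, so clustering of zBMI change within clubs is missing from the standard error of the 12-month contrast

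*Protocol article*

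**What the plan says.** All places are in the protocol article.

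- **Planned statistical analysis, random effects:** the nested structure "will be modeled by including participant- and site-level random intercepts".
- **Planned statistical analysis, test:** the effect is assessed through the interaction of condition and time, and by "specifically comparing change from baseline to 12 months via a statistical contrast".
- **Planned statistical analysis, extension:** the only one offered is "A more complex covariance structure for repeated measures over time on participants", with an unstructured form as the example, to be used if it proves necessary. No site-by-time or site-slope term is named.
- **Statistical approach and power:** "We assume an intra-class correlation coefficient of 0.05", used together with a 12-month difference of 0.1 and an SD of 0.15.
- **Study design:** clubs are the unit of randomisation: "One site within each stratum will be randomly assigned to the intervention and the other to a wait-list, usual care condition".

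The secondary outcomes are to be analysed by similar methods.

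**The concern.** The treatment effect is a difference in change, and clubs, not children, are randomised. Its standard error must therefore include how much clubs differ from one another in their average change. A random site intercept captures only how much clubs differ in level. That difference drops out once baseline is subtracted from month 12, and the contrast is then judged against within-child variation, as if children had been randomised individually. Anything that moves a whole club between the two visits enters the estimated effect but not its standard error.

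The random effects are stated in the article, so this is not a detail left to an analysis plan that is not shown. At stake are the primary p-value and confidence interval, and by extension those for beverage intake and the parent outcomes.

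**Working it through.** **Inputs**

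- α = 0.05 and 75% retention ("With α = 0.05 and a 75% retention rate"). Two-sided testing is an assumption.
- "45 parent-child pairs per each of the 10 sites", so 45 × 0.75 = 33.75 children per site at 12 months.
- One club per arm in each stratum, read as 5 against 5 sites, or 5 × 33.75 = 168.75 children per arm.
- "We powered our analysis to detect a minimum effect size of 0.1 units over 12 months", SD 0.15, ICC 0.05. zBMI is itself expressed in population SDs, so 0.15 is plausible only as the SD of change.

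**1. The plan's own power**

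- Design effect: DE = 1 + (33.75 − 1) × 0.05 = 2.6375.
- Effective n per arm: 168.75 / 2.6375 = 63.98.
- Standard error: 0.15 × √(2 / 63.98) = 0.0265.
- Power at 0.1: Φ(0.1/0.0265 − 1.96) = Φ(1.81) = 96.5%. With a noncentral t it is about 91% on 8 df and 80.2% on 4 df.
- Power at 0.2: above 99.9% by the normal approximation.

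The stated powers of over 80% and over 90% are reproduced, with clustering charged to the 12-month difference.

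**2. What the planned model does with clustering**

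For child i in site j at visit t, the model is Y = fixed part + s(j) + p(ij) + e(ijt). The change from baseline to month 12 is a fixed part + e(ij,12) − e(ij,0). Both intercepts have gone. An unstructured covariance for e changes the within-child terms but adds no correlation between children of the same site.

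If children in one club do share part of their change, with ICC ρ of change, the true variance of an arm's mean change is σ²[1 + (m − 1)ρ]/(5m). The model works with about σ²/(5m). The standard error is too small by √DE, and

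type I error = 2[1 − Φ(1.96/√DE)].

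At ρ = 0.05, the standard error in use is 0.15 × √(2/168.75) = 0.0163, against a true value of 0.0265. The ratio is 1.62.

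**3. Type I error by ICC of change, m = 33.75**

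| ICC of change | DE | √DE | Type I error |
|---|---|---|---|
| 0 | 1.000 | 1.00 | 5.0% |
| 0.005 | 1.164 | 1.08 | 6.9% |
| 0.01 | 1.328 | 1.15 | 8.9% |
| 0.02 | 1.655 | 1.29 | 12.8% |
| 0.05 | 2.638 | 1.62 | 22.8% |

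With all 45 children per site retained, ρ = 0.05 gives DE = 3.2 and 27.3%.

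**4. Simulation under no effect**

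Settings: 10 sites, 34 completers each, four visits, 5,000 trials per setting, change ICC 0.05, three shapes of club drift.

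- Random intercepts only: 23.4% to 23.9% rejections.
- Unstructured participant covariance: 22.9% to 23.4%.
- t test on site mean changes, 8 df: 5.1% to 5.3%.

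Fitted mixed models gave 20.7% (734 trials) and, with 25% dropout, 24% (116 trials, so imprecise).

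**The case against.** **The size is conditional.** A reader might infer that the true type I error simply is 20% or more. The article does not support that. It does not say whether 0.05 refers to zBMI level or to its change, and the sources cited for it are not at hand. If it describes level and change is hardly clustered, the error could be close to 5%. This objection stands, and the size has to be given as a range. It does not remove the gap: an ICC of level alone would not belong in a calculation for change, so the power section and the model need reconciling on either reading.

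**The design limits club drift.** Comparison assessments are timed to match the intervention cycles, comparison clubs refrain from obesity-specific programmes, and trained staff average two measurements. These steps may make the ICC of change smaller. They do not make it zero, and the model would not detect it if they failed.

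**Variance that grows with time.** A reader might add that random intercepts force the 2-month and 12-month changes to have equal variance, and count further inflation for that. The article already allows an unstructured participant covariance where needed, so this is not a fault of the plan.

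**Degrees of freedom.** The article names no method, and that is commonly left to the analysis plan. Its absence is not an error. It appears below only as part of the remedy.

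**Conclusion.** The point holds as a defect in the stated model: clustering of zBMI change within the randomised clubs is absent from the standard error of the primary contrast, and the permitted extension cannot bring it in. The mechanism follows from the text and needs no assumption about size.

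The size does need one. Type I error is about 23% if the plan's ICC of 0.05 is the ICC of 12-month change, about 9% to 13% at 0.01 to 0.02, and 5% only without clustering of change. These figures assume two-sided testing, 5 against 5 sites, and equal sites of 33.75 retained children.

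Nothing here says that the trial is too small. The stated power is reproduced with clustering included. The fault lies in an analysis that omits what the sample size allows for.

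**What to change.** - Add a random site-by-time effect to the primary model, or analyse site-level change.
- Test the 12-month contrast with degrees of freedom based on the number of sites, for example Kenward-Roger, about 8.
- State in advance whether strata are analysed as pairs, which leaves about 4.
- Say whether the ICC of 0.05 is for change or for level.
- Use the same model for the secondary outcomes.

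With ten sites the site-by-time variance may be estimated as zero, which would bring the narrow standard error back. The plan should say what is done then, for example that the site-level analysis is reported.

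The cost is wording and wider intervals. At a change ICC of 0.05 the 95% half-width goes from 1.96 × 0.0163 = 0.032 to 2.306 × 0.0265 = 0.061 on 8 df. Power at 0.1 units is then about 91%. On 4 df it is 80.2%, if pairing brings no gain in precision, so the claim of over 80% survives with almost no margin. No additional participants are needed.

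### The primary model defaults to random intercepts, with unstructured covariance only conditional: if zBMI change spreads out over time and the fallback is not used, the 12-month standard error is understated

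*Protocol article*

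**What the plan says.** All of this is in the Protocol article. Under Planned statistical analysis, the nesting of repeated measures within youth and of youth within sites "will be modeled by including participant- and site-level random intercepts". The next sentence is the only provision for anything richer: "A more complex covariance structure for repeated measures over time on participants (e.g. unstructured covariance) will be incorporated into the analysis if necessary". It concerns participants only; no site-by-time term is named. Intervention effects are tested through the condition-by-time interaction and "by specifically comparing change from baseline to 12 months via a statistical contrast", which corresponds to the primary outcome, change in child zBMI over 12 months.

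Under Study design, participants "complete in-person study assessments at baseline, 2, 6, and 12 months follow-up", so the visits are unequally spaced. The same section describes the trial as unblinded and says of the randomization: "One site within each stratum will be randomly assigned to the intervention and the other to a wait-list, usual care condition". Statistical approach and power gives "45 parent-child pairs per each of the 10 sites", an intra-class correlation of 0.05, an SD of 0.15 and 75% retention. The article gives no variances or correlations of zBMI by visit.

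**The concern.** A participant random intercept with independent residuals implies compound symmetry: a change over 2 months is taken to be as variable as a change over 12. The contrast that carries the primary outcome is then tested with a residual variance pooled over all intervals. Children aged 9-12 are growing, and it is plausible that their zBMI paths drift apart. If they do, the 0-12 change is the most variable of all, and pooling it with shorter intervals gives a confidence interval that is too narrow and a p-value that is too small.

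The stated remedy is conditional. Whether it is used would be decided from the outcome data, so the primary standard error is not fixed in advance. Separately, the site intercept does nothing for a change contrast: in complete data it cancels. Variation between sites in change therefore goes uncounted unless a further term is added.

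**Working it through.** **Inputs.** Visits at 0, 2, 6 and 12 months, 10 sites, 45 pairs per site, 75% retention, ICC 0.05, SD 0.15 and alpha 0.05 come from the article. Assumptions: a two-sided test; 0.15 is the SD of 12-month change (the text does not say which SD it is); the pattern of zBMI variance over time, varied below.

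**1. The plan's own figure.** Retained children per site: 45 × 0.75 = 33.75. Design effect: 1 + 32.75 × 0.05 = 2.64. Effective n per arm: 225 × 0.75 / 2.64 = 64. Standard error: 0.15 × √(2/64) = 0.0265. Power for 0.1 is 96.5% with a normal reference, 90.9% with t on 8 df and 80.2% with t on 4 df (stratified). The stated power of over 80% is reproduced. That calculation charges the full site-level design effect to the comparison.

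**2. What the intercept-only model does at child level.** With complete data, its variance for any change is the mean of the six pairwise change variances. The SE ratio is √(model variance / true 0-12 variance), and type I error is 2 × [1 − Φ(1.96 × SE ratio)]. Only the shape of the covariance matters, not the value 0.15.

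- *All random walk.* Pairwise variances are proportional to 2, 6, 12, 4, 10 and 6, with mean 40/6 = 6.67 against 12 for months 0-12. Variance ratio 0.556, SE ratio 0.745, type I error 14.4%.
- *Half random walk, half visit noise.* Variance ratio 0.5 × 0.556 + 0.5 = 0.778, SE ratio 0.882, type I error 8.4%.
- *Compound symmetry.* Ratio 1, type I error 5.0%.
- *Noisier middle visits* (residual variances 0.010, 0.015, 0.015, 0.010). Model variance 2 × 0.0125 = 0.025 against a true 0.020. SE ratio 1.118, type I error 2.8%.
- *Random slopes*, as a sensitivity check. With 50% of the change variance from slopes: SE ratio 0.833, type I error 10.2%. With 100%: 0.624 and 22.2%.

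**3. The two-step plan as written.** The article names no selection criterion, so AIC and BIC are assumed here. Simulation with 338 completers, no site effects and 4,000 runs per case:

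| Random-walk share | Unstructured chosen (AIC / BIC) | Type I, intercept only | Type I, AIC switch | Type I, BIC switch |
|---|---|---|---|---|
| 0.99 | 100% / 100% | 14.1% | 5.3% | 5.3% |
| 0.75 | 100% / 100% | 10.9% | 4.4% | 4.4% |
| 0.50 | 99.9% / 56% | 7.9% | 4.9% | 6.0% |
| 0.25 | 46% / 0.1% | 5.8% | 5.2% | 5.8% |

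Further runs that included likelihood-ratio selection and random slopes gave about 4-6%, and 7.4% at worst (BIC with a random slope).

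**4. The site level.** If sites differ in change and only a site intercept is fitted, the SE ratio is 1/√[1 + 32.75 × ICC of change]. An ICC of 0.01 gives 0.868 and type I error 8.9%; 0.05 gives 0.616 and 22.8%. Simulation (10 sites of 34 children, complete data, 4,000 runs; child-level change as pure noise / half random slope):

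| ICC of change | Unstructured participant covariance + site intercept | Site-level t-test, 8 df |
|---|---|---|
| 0 | 4.9% / 5.9% | 4.9% / 4.7% |
| 0.01 | 9.6% / 9.8% | 4.9% / 5.3% |
| 0.05 | 22.1% / 23.5% | 4.8% / 5.0% |

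**The case against.** The strongest reply is that the plan does not stop at random intercepts. It names unstructured covariance as the likely refinement, and step 3 shows that a competent fit-based switch removes most of the inflation: where the intercept-only error would be serious, AIC and BIC both choose unstructured. This stands. A reader might infer that the trial will run its primary test at 14% or more. The documents do not support that, because the figure requires the fallback to be ignored.

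Second, the direction of the error is not established. A reader might take it as given that the default makes the standard error too small. Without visit variances, that is conditional: there is no error under compound symmetry, and the error reverses with noisier middle visits. This also stands.

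Third, the selection rule and the convergence fallback are ordinary analysis-plan content, and that plan is not shown. This stands too, so the absence of a rule is not itself the point. The point is what the article does fix: a restrictive default, with the safer structure conditional, for the contrast that matters most.

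Fourth, a reader might infer that the covariance would be chosen with the treatment effect in view. The trial is unblinded, but nothing says so, and covariance fit can be judged without arm labels. What remains is narrower: the choice would still depend on outcome data.

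Finally, changing the participant covariance alone would not secure the test. Step 4 confirms this, and the fix takes it in.

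**Conclusion.** The point holds as a conditional weakness in the stated default and is best labelled a cheap improvement. If the variance of zBMI change grows with time and the fallback is not used, type I error for the 12-month contrast is about 8% (half random walk) to 14% (all random walk); steeper patterns such as random slopes go higher. With a fit-based switch it is about 5-7%, and what is lost is mainly that the primary standard error is no longer fixed in advance.

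The child-level figures assume complete data, no site differences in change, and covariance patterns that the article neither states nor rules out. The site-level figures depend on the ICC of change. The article assumes 0.05 for its sample size without saying whether this refers to the level of zBMI or to its change. If it applies to change, unstructured participant covariance with only a site intercept leaves type I error at 22-24%.

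**What to change.** In Planned statistical analysis, state that the primary model uses an unstructured participant-level covariance over the four visits in place of the participant random intercept, and delete the clause that makes it conditional on need. Give a fixed order of simpler structures to use if it fails to converge. In the same sentence, specify a site-by-time random effect, or a site-level analysis of change, with small-sample degrees of freedom.

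The cost is wording and slightly more analysis work. Four visits need 4 × 5 / 2 = 10 covariance parameters, easily estimated from 450 children. The interval will be somewhat wider. On the article's own inputs, power for 0.1 is still 90.9% with 8 df and 80.2% with 4 df. If the design effect uses the enrolled 45 per site rather than the retained 33.75, these become 84.9% and 72.7%, so the choice of degrees of freedom should be made explicitly.
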